## Abstract

**Background:**

Although evidence shows the positive health effects of physical activity, most of the adult population in Colombia are sedentary. It is, therefore, important to implement strategies that generate changes in lifestyle behaviours. This protocol describes a study in which we will compare the effects of 12 weeks of high-intensity interval training (HIIT), resistance training (RT) or combined training (HIIT + RT) on the improvement of body composition, endothelial function, blood pressure, blood lipids, and cardiorespiratory fitness in a cohort of sedentary, overweight adults (aged 30–50 years).

**Methods/design:**

Sixty sedentary, overweight adults attending primary care in Bogotá, Colombia will be included in a factorial randomised controlled trial. Participants will be randomly assigned to the following intervention groups: (1) non-exercise group: usual care with dietary support, (2) HIIT group: 4 × 4-min intervals at 85–95 % maximum heart rate (HRmax) (with the target zone maintained for at least 2 minutes), interspersed with a 4-min recovery period, at 65 % HRmax, (3) RT group: completing a resistance circuit (including upper and lower muscle groups) as many times as needed according to subject’s weight until an expenditure of 500 kcal at 40–80 % of one-rep max (1RM) has been achieved, and (4) combined group: HIIT + RT. The primary end point for effectiveness is vascular function as measured by flow-mediated vasodilatation 1 week after the end of exercise training.

**Discussion:**

The results of this study will provide new information about the possible effect of the programme in improving the cardiometabolic health of overweight adults, making a more efficient use of an adult’s resources over time.

**Trial registration:**

ClinicalTrials.gov ID: NCT02715063. Registered on 8 March 2016.

**Electronic supplementary material:**

The online version of this article (doi:10.1186/s13063-016-1422-1) contains supplementary material, which is available to authorized users.

## Background

The prevalence of obesity has increased worldwide [1] among both children and adults, and obesity is associated with an increased risk for cardiovascular diseases (CVD) [2, 3]. Substantial evidence indicates that increased body weight and body fat distribution are associated with a higher frequency of adverse health consequences, including hypertension, CVD, metabolic disorders, osteoarthritis, gallbladder stone disease, asthma and multiple malignancies [4, 5]. International organisations [6, 7] and previous epidemiological cross-sectional studies have suggested that individuals with a large accumulation of body fat in the abdominal region are at greater risk for the development of metabolic syndrome [8, 9]. In addition to obesity, hypertension, dyslipidaemia and low cardiorespiratory fitness (CRF) are also modifiable risk factors associated with the risk for CVD [10, 11]. Furthermore, it has become increasingly clear that low CRF may exacerbate the risk of CVD mortality, and that increasing peak CRF to higher than 5 peak metabolic equivalents (MET) can reduce and perhaps eliminate the mortality rate associated with dyslipidaemia, obesity, type 2 diabetes mellitus and hypertension [12].

The health benefits of exercise training are well documented; it is necessary for healthy growth and development because it optimises cardiometabolic function and prevents chronic disease [13, 14]. Additionally, its benefits are not only biological, but also include psychosocial advantages [15]. The most recent guidelines promoted by the World Health Organisation (WHO) recommend a minimum of 150 min of moderate-intensity physical activity (3 to <6 MET) or 75 min of vigorous-intensity physical activity (≥6 MET per week or any equivalent combination for health benefits, and 300 min of moderate-intensity physical activity or 150 min of vigorous-intensity physical activity per week for additional health benefits [16, 17].

Previous studies have reported improvement in endothelial function in different disorders, such as obesity, diabetes mellitus and metabolic syndrome, by increasing the production and bioactivity of nitric oxide [18–21]. In addition, a growing body of evidence has demonstrated comparable or superior improvements in cardiometabolic health outcomes using low-volume, high-intensity interval training (HIIT) compared to traditional moderate-intensity continuous training (MICT) [18, 19]. Other studies have revealed a strong relationship between vascular function and CRF [20, 21]. Thus, because HIIT is a potent method of improving CRF, several systematic and narrative reviews that have investigated the impact of HIIT relative to MICT on vascular function in clinical patients have emerged over recent years [18, 19, 22]. HIIT provides rapid physiological adaptations, as indicated by improvements in maximal oxygen uptake (VO_2_max), anaerobic threshold and stroke volume [23, 24]. Instead, it was suggested that the ability of HIIT to restore vascular homeostasis through enhancement in shear stress-induced nitric oxide bioavailability may be another important mechanism that explains the protective role of exercise against CVD development [25].

Interestingly, despite the prevalence of obesity and the existing multiple position stands promoting exercise for the treatment of obesity, there are few randomised trials that have directly compared the effects of sustained resistance training (RT), HIIT, or a combination of the two (RT + HIIT) to be as effective or more effective for improving cardiometabolic health in adults [26, 27]. Most of the published studies addressing RT and fat mass changes have compared RT to an inactive control group and not to HIIT. Furthermore, existing studies have not directly studied comparable amounts of HIIT and RT. A recent randomised controlled trial (RCT) suggests that adding plyometric exercises to a HIIT programme may be more beneficial than HIIT alone in young obese women [28]. Given the increasing burden of chronic disease, more research is needed to better understand the effect of different exercise modalities on these risk factors [29].

Thus, this paper describes the rationale, design, and methodologies used in a factorial randomised controlled trial (Cardiometabolic HIIT-RT Study), wherein we hypothesised that HIIT and combined training would result in greater improvements in vascular function compared to RT and usual clinical care.

## Methods/design

### Study design and setting

The present study is a RCT (ClinicalTrials.gov ID: NCT02715063). The Cardiometabolic HIIT-RT Study is a single-blind, randomised controlled, 2 × 2 factorial trial. The study received ethical approval from the Medical Research Ethics Committee of The University of Manuela Beltran (ID 06-1006-2014). Random allocation to treatment will be performed at the individual level.

### Procedures

#### Participants

Participants aged 30–50 years, who are sedentary (no participation in exercise more than once a week for the previous 6 months) with abdominal obesity: waist circumference (WC) at least 90 cm for men, and at least 80 cm for women, or with excess weight: body mass index (BMI) at least 25 kg/m^2^ for men and 35 kg/m^2^ for women, and who are identified as being willing and with almost immediate availability, will be enrolled. Eligible subjects for the present study and those interested in participating will be invited to a pre-test that includes an interview in a private health care institution (Clinica Rangel Pereira IPS) and further assessments performed at the Centre of Studies in Physical Activity Measurements (in Spanish, CEMA), School of Medicine and Health Sciences, University of Rosario, Bogotá, Colombia. Risks will be minimised by ruling out contraindications to the testing and training protocols via a health history and thorough physical examination prior to the testing sessions. Inclusion and exclusion criteria are provided in Table 1.

**Table 1 Tab1:** Inclusion/exclusion criteria

Inclusion criteria	Exclusion criteria
Central obesity: waist circumference ≥90 cm (men); ≥80 cm (women), or with excess weight: body mass index ≥25 kg/m^2^ (men) and ≤ 35 kg/m^2^ (women)	Systemic infections
Meets at least one criteria for metabolic syndrome (IDF 2006): triglycerides ≥150 mg/dl; HDLc <40 mg/dL (men); <50 mg/dL (women); high blood pressure ≥130/85 mmHg and/or fasting plasma glucose ≥100 mg/dL	Weight loss or gain of >10 % of body weight in the past 6 months for any reason
Written informed consent	Currently taking medication that suppresses or stimulates appetite
Interested in improving cardiovascular health and physical fitness	Uncontrolled hypertension: systolic blood pressure 160 mmHg or diastolic blood pressure 95 mmHg on treatment
	Gastrointestinal disease, including self-reported chronic hepatitis or cirrhosis, any episode of alcoholic hepatitis or alcoholic pancreatitis within the past year, inflammatory bowel disease requiring treatment within the past year, recent or abdominal surgery (e.g. gastrostomy)
	Asthma
	Diagnosed diabetes (type 1 or 2), fasting impaired glucose tolerance (blood glucose 118 mg/dL), or use of any antidiabetic medications
	Currently taking antidepressant, steroid, or thyroid medication, unless dosage unstable (no change for 6 months)
	Current exerciser (>30 min organised exercise per week).
	Indication of unsuitability of current health for exercise protocol (Physical Activity Readiness Questionnaire, PARQ)
	Any other conditions which, in the opinion of the investigators, would adversely affect the conduct of the trial

#### Recruitment

Consecutive men or women with abdominal obesity or excess weight will be recruited from a private health care institution (Clinica Rangel Pereira, IPS) and one primary care institution (Universidad del Rosario, IPS) that receives referrals from both medical consultants in secondary care and primary care general practitioners in the capital district of Bogotá, Cundinamarca Department in the Andean region. This region is located at approximately 4°35′56″N 74°04′51″W and at an elevation of approximately 2625 m (min: 2500 m; max: 3250 m) above sea level [30]. Subjects who are interested in participating will be approached with further information and screened for pre-participation exercise habits using a cardiovascular and musculoskeletal checklist (i.e. the patient’s medical history, disease history, physical fitness, and more). A member of the research team will follow up with a phone call to screen for eligibility and explain the main requirements of the study. All participants will provide written informed consent before entering the study.

#### Blinding and randomisation methods

The randomisation into the four study arms will be performed by the Centre of Studies in Physical Activity Measurements at University of Rosario, Bogotá, Colombia, using block randomisation with a block size of four. Eligible participants will be randomly assigned after completing the baseline measurements to either the control or exercise training groups. The principal investigator will coordinate the allocation sequence, and randomisation will be computer-generated. All participants and study personnel (including investigators, trainers, and statisticians) will be blinded to treatment allocation throughout the trial protocol. Access to the allocation code will be restricted to one study statistician who will not perform the final study analyses. Randomisation will be conducted independently using sealed opaque envelopes. These procedures are also detailed in the study operations manual. Moreover, the importance of maintaining the blinding and allocation concealment will be reinforced by regularly scheduled conference calls at the sites and daily meetings with the field investigators (Fig. 1).

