#### Statistical analyses

The final data will be analysed using IBM SPSS 22.0 (SPSS, Inc., Chicago, IL, USA) and SAS software (SAS Institute Inc., Cary, NC, USA). An exploratory analysis will be performed to determine the frequency, range, variability, and distribution type for each variable to use the most appropriate statistical test when comparisons will be necessary. These analyses permit the assessment of the primary analysis of the data and will be undertaken using the principle of intention-to-treat (ITT). The ITT analysis for this study will include all participants, including those who are not fully compliant and those with missing outcome data. Because this is an experimental design with two measures of the primary and secondary outcomes, the first at baseline x0 (t0 = weeks) and the second after interventions x1 (t1 = 12 weeks) in four study groups, a comparative analysis between these measures to establish differences will be executed. To perform these comparisons, one-way ANOVA or Kruskal-Wallis tests will be applied when appropriate. Subsequently, a multivariate analysis will be carried out, and the autocorrelation between repeated measures will be taken into account. We will use longitudinal analysis methods, such as a generalised estimating equation approach, to control the differences among measures at baseline and to incorporate incomplete observations into this analysis. Finally, we will investigate if there is an interaction between the two interventions for the primary outcome at 12 weeks of supervised training HIIT, RT or combined training (HIIT + RT). For these analyses, we will include appropriate interaction terms in the models [38, 65]. The trial is not powered to detect these interactions and is likely to have poor precision for the interaction terms. We plan to report regression coefficients for the interaction terms and their 95 % confidence intervals. However, we aim to recruit 15 participants per group (a total of 60) to accommodate for a 20 % attrition rate and elimination due to non-compliance.

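### One fixed block size of four for four arms is the most predictable permuted-block scheme for this design; to an observer who knows past allocations, up to 15 of 60 assignments are determined

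*Protocol article*

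**What the plan says.** The Blinding and randomisation methods section of the protocol article states: "The randomisation into the four study arms will be performed by the Centre of Studies in Physical Activity Measurements", "using block randomisation with a block size of four". No second block size and no stratification factor is mentioned. Study design and setting adds: "Random allocation to treatment will be performed at the individual level". The target is 15 participants per group, 60 in total (Statistical analyses).

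On concealment, the randomisation section provides for sealed opaque envelopes and for assignment once baseline measurements are complete. It also says: "Access to the allocation code will be restricted to one study statistician who will not perform the final study analyses". Just before that it says: "The principal investigator will coordinate the allocation sequence, and randomisation will be computer-generated".

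On blinding it states: "All participants and study personnel (including investigators, trainers, and statisticians) will be blinded to treatment allocation throughout the trial protocol". Study design and setting, however, describes a "single-blind, randomised controlled, 2 × 2 factorial trial".

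**The concern.** When the block size equals the number of arms, each block is a permutation of the arms. Anyone who has seen the first three allocations of a block knows the fourth. An opaque envelope hides its own contents, but it does not hide what can be deduced from the envelopes already opened.

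This matters only if past allocations are visible, which the protocol denies in one place and makes implausible in others. The Intervention section describes treadmill intervals, a resistance circuit, both, or no training. Sessions are supervised in an exercise laboratory, in groups of at most three to five. Trainers and participants cannot be unaware of the arm, and single-blind in the design section does not fit the blanket statement in the randomisation section. That past allocations are visible to staff is therefore an inference from these passages, not something the protocol states.

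What is at stake is who enters and in what order. Table 1 lets investigators exclude a candidate for any other condition that they judge would harm the conduct of the trial, so entry is partly discretionary. With 15 per arm, selection on unmeasured features such as motivation could shift the composition of the arms.

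**Working it through.** The protocol gives no predictability figure, so there is none to reproduce.

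**Inputs.** Arms k = 4 and block size b = 4 (Blinding and randomisation methods); N = 60, 15 per arm (Statistical analyses). Each block holds b/k = 4/4 = 1 participant per arm, and there are 60/4 = 15 blocks. Four is the smallest block that can balance four arms.

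**Observer.** Knows every earlier allocation in order, and where each block starts.

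**1. Fully determined.** Only position 4 of each block: 15 × 1 = 15 of 60 = 25%.

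**2. Correct guesses.** The chances at positions 1 to 4 are 1/4, 1/3, 1/2 and 1.
- Mean: (1/4 + 1/3 + 1/2 + 1)/4 = 0.521.
- Per trial: 15 × (1/4 + 1/3 + 1/2 + 1) = 31.25 of 60.
- By chance alone: 25%, or 15 of 60.

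**3. Usual care or exercise known with certainty.** This holds if usual care has already been used in the block, or if only one place is left. The chances at positions 1 to 4 are 0, 1/4, 1/2 and 1, so (0 + 1/4 + 1/2 + 1)/4 = 7/16 = 43.75%.

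**4. Fixed blocks of eight, for comparison.** Position 8 is always determined, and position 7 is determined with probability 1/7.
- Complete blocks: (1 + 1/7)/8 = 14.3% determined.
- At N = 60 there are 7 complete blocks and a half block with nothing determined: 7 × 8/7 = 8 of 60 = 13.3%.
- Usual-care status certain in complete blocks: (2 + 2/7)/8 = 28.6%.

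**5. Varying sizes.** Lists of 60 were simulated with equally likely block sizes. The observer knows the set of possible sizes but not the size of each block.

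| Scheme | Determined | Correct guesses |
|---|---|---|
| Fixed 4 (as planned) | 25% | 52% |
| Fixed 8 | 13% | 46% |
| Random 4/8, sizes hidden | 7% | 48% |
| Random 4/8/12, sizes hidden | 3% | 46% |

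If the size of each block were also known, the determined share would be 18% for 4/8 and 14% for 4/8/12. Much of the gain therefore comes from keeping the sizes hidden.

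**6. Pace.** Recruitment from March to October 2016 (Trial status) is at most 8 months: 60/8 = 7.5 participants, or about two blocks, a month. A sequence this slow is not hard to follow.

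**The case against.** The strongest reply is that the figures describe an observer whom the protocol does not document. Recruitment runs through two institutions, usual-care participants do not attend training, and nothing shows that those who screen and telephone candidates see the whole ordered sequence. This stands: the figures are upper bounds, and someone who sees one institution's allocations deduces less. A reader might infer that staff simply know every fourth assignment in advance, but the documents support only the conditional statement.

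Second, safeguards exist. Recruitment is of consecutive patients, assignment follows the baseline measurements, and the planned models control for baseline differences. These limit the risk: baseline values cannot be influenced by a predicted arm, and measured imbalance is partly handled. They do not remove selection on unmeasured factors.

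Third, a reader might infer a bias that is large relative to 15 per arm. Predictability was calculated, but bias in flow-mediated dilatation was not, and the documents give nothing from which to calculate it. A reader might also infer that the block size was public during recruitment. The text supplied gives recruitment dates but no publication date, so this cannot be confirmed.

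Fourth, the sentence about the principal investigator need not mean access to the code. To coordinate a sequence may be purely administrative. The wording is ambiguous beside the restriction to one statistician and should be clarified, but it is not evidence of a breach.

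Finally, blocks of four deliver exactly 15 per arm, which varying blocks may not. That is true, and it is the price of the change.

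**Conclusion.** The point holds as a cheap improvement to a stated rule. The protocol fixes the most predictable permuted-block scheme available for four arms, in a trial whose interventions can hardly be hidden from those who deliver or receive them. At the upper bound, 25% of assignments are determined, 52% are guessable against 25% by chance, and usual-care status is certain for 44%.

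This rests on two assumptions: that past allocations are visible, which is inferred from the design section and the nature of the arms against the blinding statement; and that one person can follow the full sequence and its block starts. No steering of entry is shown, and no size of bias is claimed. Varying the block size mainly removes certainty and lowers the overall guess rate only modestly.

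**What to change.** For any remaining allocations:
- Replace the fixed block size with randomly varying sizes, for example 4, 8 and 12, and keep the sizes from everyone who enrols participants, including in the operations manual that they use.
- Have the independent statistician generate and hold the sequence. Reword the sentence on the principal investigator's coordinating role so that it agrees with the restriction on access to the code.
- Reconcile the blanket blinding statement with the single-blind label, and say who is in fact blinded.
- Keep the opaque envelopes and assignment after baseline measurements.

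The cost is a new list and a possible end imbalance of a few participants per arm. A block of 12 holds three of each arm, so if the list stops inside one, two arms can differ by at most 3.

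If allocation is already complete, nothing can be changed. The report should then state the block scheme and who could see allocations, and name predictability as a limitation.

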#### Intervention

The participants who are randomly assigned to the intervention group will participate in the cardiometabolic programme.Usual clinical care group

This group will receive usual clinical care according to the consensus recommendations of the national goals for cardiovascular health promotion and disease reduction of the American Heart Association [31] and Colombian guidelines COLDEPORTES (in Spanish, Departamento Administrativo del Deporte, la Recreacion, la Actividad Fisica y el Aprovechamiento del Tiempo Libre) [32]. Participants will receive counselling about goals for cardiovascular health, as well as monitoring cardiovascular health over time in the Colombian population, key signs and symptoms, diet and screening for cardiometabolic risk factors. This group will be asked to maintain their level of activity during the 12-week study period.2.High-intensity interval training (HIIT) group

The HIIT protocol will be completed with fast walking or running on a treadmill with the deck inclined to reach the desired intensity. We will calculate the training energy expenditure for participants’ age ranges associated with meeting the consensus public health recommendations from the WHO [16] and the US Department of Health and Human Services [17]. Each preparatory period starts with an exercise dose of 6 kcal kg^-1^ week^-1^, which will increase progressively by 2 kcal kg^-1^ week^-1^ until week 4, where it will remain at 12 kcal kg^-1^ week^-1^ for weeks 5 to 12.

*Preparatory training phase: weeks 1–4*

To initiate our study we will use a 4-week preparatory phase of training to bring all participants up their 300-kcal goal for the session. To accomplish this they will warm up at 65 % of maximum heart rate (HRmax) (5 min); exercise for 4 × 4-min intervals at 60–80 % HRmax, interspersed with a 4-min recovery period at 55 % HRmax, at a frequency of three times per week.

*Protocol of interval training: weeks 5–12*

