After the preparatory phase, participants will expend 500 kcal of energy during the protocol training phase at 40–80 % of 1RM, for 4 × 20–30 repetitions and 1-min rest intervals. The RT protocol will be used to complete a resistance circuit (including upper and lower muscle groups; eight exercises); all participants will expend energy up to the 500-kcal goal. The entire workout will last approximately 30–40 minutes, depending on the number of exercises (Table 2), at a frequency of three times per week. Each session is preceded and followed by a gradual warm-up and cool-down period (both of 10-min duration and consisting of walking and light, static stretching (avoiding muscle pain) in most muscle groups). The cool-down period also includes relaxation and stretching exercises. The RT protocol will be performed through the full range of motion normally associated with correct technique for each exercise, engaging the major muscle groups (abdominal, dorsal, shoulder, upper and lower limb muscles). As a general rule and to avoid potential risks, we will avoid (1) activities that include Valsalva’s mechanism, (2) ballistic and plyometric movements, and (3) positions of extreme muscular tension. This resistance training programme has been used before, successfully promoting strength and muscle gains in middle-aged and elderly populations with a variety of conditions (e.g. diabetes type II and obesity) [33, 34].4.Combined training group

This group will receive both the HIIT and RT protocols as described above. Therefore, the energy expenditure associated with the physical training prescribed for the vigorous-intensity group will be approximately 1500 kcal/week.

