Overall, we will monitor each subject’s HR (FS1, Polar Electro Öy, Kempele, Finland) during the exercise sessions. We will estimate the energy expenditure during the exercise sessions by calibrating the energy expenditure to the HR during the VO_2_max tests performed at the baseline and post-intervention time points. The regression of the energy expenditure will be calculated for each participant according to HR and minutes spent exercising during the training sessions. Trainers will be physical therapists and physical educators with experience developing and monitoring exercise programmes among clinical populations. All protocol training will be performed under observation and supervision in an exercise laboratory with complete and strict monitoring of the amount of exercise completed in each session. Adherence to the exercise programme will be encouraged by the exercise professional who supervises each of the group sessions. To maximise adherence to the training programme each session will have a maximum of three to five participants training simultaneously. Attendance at supervised sessions includes compliance with target HR and expenditure energy and will be monitored and recorded by research staff. Each participant will meet with the study dietician for nutrition assessment and counselling, and an individualised nutrition intervention plan will be developed from the baseline food intake assessment according to participant preferences [35]. This plan is a standardised meal consisting of 1300 to 1500 kcal (50–55 % carbohydrates, 30–35 % total fat, less than 7 % saturated fat and 15–22 % protein).

At the beginning of the training protocol, we will obtain the participants’ weight to determine weekly energy expenditure necessary to achieve their target of 12 kcal kg^-1^ week^-1^ (iso-energetic). It is expected that the gradual increase in total energy expenditure will minimise fatigue, soreness, injuries, and attrition.

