### Data collection and outcome measures

Outcome measures will be assessed at baseline and at 12-week follow-up by personnel blinded to the treatment allocation. Data will be recorded on standardised forms and entered into a secured-access database that contains quality control checks (e.g. range checks, notification of missing data).

The primary outcome measure is endothelial function as measured by flow-mediated dilatation (FMD). The secondary outcome variables include HR variability, pulse wave velocity (PWV), weight, BMI, WC, body composition, body temperature, biochemical profile, health-related physical fitness, self-perceived health, health-related quality of life (HRQL), and side effects. Other variables of interest include 24-hour dietary recall, lifestyle and demographic characteristics (Table 3 and Figure 3).

**Table 3 Tab3:** Summary of time point measurements of the primary and secondary outcomes of the study

Type of outcomes	Specific outcomes	Measurements		
		1-baseline (week 0)	2-moment (week 4)	3-moment (week 12)
Primary outcomes	Endothelial function as measured by flow-mediated vasodilatation	X		X
Secondary outcomes	Vascular function: heart rate variability, aortic pulse wave velocity, augmentation index and blood pressure	X		X
	Morphological component: weight, height, BMI, waist circumference	X	X	
	Body composition: fat mass and non-bone lean body mass	X		X
	Body temperature	X		X
	Plasma samples and biochemical analysis: LDL cholesterol (LDL-c), HDL cholesterol (HDL-c), total cholesterol, triglycerides, glucose, glycated haemoglobin (HbA1c)	X		X
	Fitness component: self-reported fitness, 1RM, hand-grip and peak uptake of volume of oxygen	X		X
	Self-perceived health: health-related quality of life	X		X
	Recent Physical Activity Questionnaire	X	X	X
	Demographic information	X		
	Side effects	X	X	X

*1RM* one repetition maximum, *BMI* body mass index

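### Participants and trainers are declared blinded to openly different, supervised exercise arms; this cannot hold, contradicts the single-blind label, and bears on self-reported and effort-dependent secondary outcomes

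*Protocol article*

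**What the plan says.** Four parts of the protocol article bear on who knows the allocation.

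- **Blinding and randomisation methods.** The general statement is "All participants and study personnel (including investigators, trainers, and statisticians) will be blinded to treatment allocation throughout the trial protocol". The same paragraph gives the principal investigator the task of coordinating the allocation sequence. It limits access to the code to one statistician, who does not run the final analyses. It adds that calls and meetings will reinforce blinding and concealment.
- **Study design and setting.** The trial "is a single-blind, randomised controlled" design. The party that is blind is not named there.
- **Intervention.** For usual care: "This group will be asked to maintain their level of activity during the 12-week study period". For HIIT: "The HIIT protocol will be completed with fast walking or running on a treadmill". For RT: "The RT protocol will be used to complete a resistance circuit (including upper and lower muscle groups; eight exercises". The combined arm receives both programmes. On delivery: "All protocol training will be performed under observation and supervision in an exercise laboratory".
- **Data collection and outcome measures**, and the sections on single outcomes. Outcomes are assessed "by personnel blinded to the treatment allocation". The FMD images are read by one blinded observer, and the DEXA technologist is blinded to the randomisation.

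**The concern.** A participant knows whether he or she runs intervals, lifts weights, does both or does neither. A trainer cannot deliver and record a session without knowing which programme it belongs to. The blinding statement therefore describes a property that the trial does not have for these two groups.

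At stake is how the secondary results may be read. Several rest on what participants say about their fitness, health, activity or side effects, and others depend on how hard they try. Knowledge of the arm can move both kinds of result, whoever takes the measurement. Taken at face value, the blinding statement tells a reader that this source of bias is closed when it is open.

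**Working it through.** The document gives no figure to reproduce and no arithmetic is needed. The check sets the passages side by side.

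**1. Can participants be blinded?** The Intervention section describes four experiences that are plainly distinct: keeping to one's usual activity, treadmill intervals, an eight-exercise resistance circuit, or both programmes. No sham or attention-control exercise is described. All 60 planned participants (four groups of 15) would know what they are doing. The statement fails for participants.

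**2. Can trainers be blinded?** Training takes place under supervision in an exercise laboratory, and staff record attendance and compliance with heart-rate and energy targets. The trainer sees the programme at every session. The statement fails for trainers.

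**3. Can investigators and statisticians be blinded?** In part. An investigator with no role in delivery could be, but the one who coordinates the allocation sequence is poorly placed to be. The analysing statistician can be, because another statistician holds the code. That second statistician is by definition not blinded. The statement, which covers all of them, conflicts with its own paragraph.

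**4. Does it agree with the design label?** No. Blinding participants, investigators, trainers and statisticians is more than single-blind on any usual reading. If the blinded party is the outcome assessor, single-blind fits the rest of the article, and the blinding statement is the outlier.

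**5. Does other text narrow the statement?** No. It is not limited to assessors or to knowledge of the study hypothesis. Its reach over the whole trial, and its naming of trainers, rule out reading it as allocation concealment alone.

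**6. Which outcomes are exposed?**

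| Outcome | What the article provides | Exposure to participants knowing their arm |
|---|---|---|
| FMD (primary) | Blinded assessors; blinded image reader | Low, covered on paper |
| Body composition by DEXA | Blinded technologist | Low |
| IFIS, SF-12, RPAQ, side effects | Depend on participant report | Direct |
| VO2max | Two of three criteria for a maximal test, but the test ends at fatigue | Present, reduced |
| Hand-grip | No verbal encouragement | Present, reduced |
| 1RM | Predicted from repetitions to fatigue in the preparatory training phase | Present; also a question of who assesses |

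**7. A related gap.** Outcomes are to be assessed by blinded personnel, yet Health-related physical fitness predicts 1RM from performance in the preparatory phase, which is supervised training. Because the article counts trainers as blinded, nothing in it separates them from this assessment.

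**The case against.** The strongest defence is that the blinding that matters most is already in place. Assessors are blinded for all outcomes, one blinded observer reads the FMD images, the DEXA technologist is blinded, and the code is kept from the analysing statistician. The article calls the trial single-blind, so it does not consistently claim full blinding. On this view the sentence is loose wording with no effect on the sample size, the primary assessment or the primary analysis.

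Most of this stands, and it rules out several stronger readings that a reader might infer:

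- *The primary outcome is compromised.* The documents do not support this. The commitment to blinded assessors covers the FMD scan, and the reader is separately blinded.
- *Blinding is impossible for everyone named.* It is impossible for participants and trainers. Investigators outside delivery and the analysing statistician can be blinded.
- *The false claim removes the incentive to protect the blinding that is possible.* The same paragraph commits to reinforcing blinding through calls and meetings.
- *The results will be presented as fully blinded.* The article nowhere says so. This is an inference from the sentence, and only for secondary outcomes.
- *Effort-dependent tests are as exposed as questionnaires.* The VO2max criteria and the rule against encouragement in hand-grip testing reduce the risk, though they do not remove it.

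The defence does not rescue the sentence itself. It is an explicit statement, not a detail left out of a condensed article, and it is untrue for two of the groups it covers.

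**Conclusion.** The point holds. The blinding statement is untenable for participants and trainers, contradicts the single-blind label, and conflicts with the roles given to the principal investigator and to the statistician who holds the code.

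The consequence is limited to secondary outcomes. Four that rest on participant report are directly exposed, and three effort-dependent ones to a lesser degree. No size of bias can be given, because the article has no figures from which to derive one. The conclusion rests on the arms being delivered as described, with no sham, and on the commitments to blinded assessors and a blinded reader being kept.

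**What to change.** Replace the sentence with a statement along these lines: participants and trainers are not blinded; outcome assessors, including the FMD sonographer, the FMD image reader and the DEXA technologist, are blinded, as is the statistician who performs the final analyses. Then:

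1. Say in Study design and setting that single-blind refers to these assessors, so that the two sections agree.
2. Describe the principal investigator and the code-holding statistician according to their roles, and do not list them as blinded.
3. State that trainers do not assess outcomes and that participants are asked not to reveal their group to assessors.
4. Reconcile item 3 with Health-related physical fitness, where 1RM is predicted from performance in the supervised preparatory phase. Say who obtains that measurement and whether that person knows the arm.
5. Report IFIS, SF-12, RPAQ, side effects, VO2max, hand-grip and 1RM as obtained from unblinded participants.

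The cost is a less favourable but accurate description of blinding, plus the two procedural instructions in item 3, which the article does not now contain. The sample size and the primary analysis are unchanged.
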